**Methods:**

Participants will consist of approximately 840 year 9 or year 10 students (60 students per grade per school) from 14 New South Wales high schools in Sydney, Australia. Schools will be recruited from a random selection of independent and public schools across the New South Wales Greater Sydney Area by using publicly available contact details. The intervention will consist of 1 introductory classroom lesson and a downloadable mobile app that will be available for use for 12 months. Schools will be randomly allocated to receive either the mHealth peer intervention or a waitlist control (health education as usual). All students will be given web-based self-assessments at baseline and at 6- and 12-month follow-ups. The primary outcomes of the trial will be the self-reported use of alcohol and drugs, anxiety and depression symptoms, knowledge about mental health and substance use, motives for not drinking, and willingness to seek help. Secondary outcomes will include positive well-being, the quality of life, and the impact of the COVID-19 pandemic. Analyses will be conducted using mixed-effects linear regression analyses for normally distributed data and mixed-effects logistic regression analyses for categorical data.

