### Sample Size Calculations

This trial is powered to detect intervention by time interactions in longitudinal cluster RCTs. To allow for comparisons between the two conditions, 6 schools (with at least 60 students) in each of the 2 intervention groups were required, giving a total of 12 schools (with at least 720 students). This would achieve 80% power to detect a standardized between-group mean difference of 0.2 in outcomes at the end of the trial with three measurement occasions (*P*=.05). An effect size of 0.2, which is comparable with previous trials of anxiety, depression, and substance use prevention programs [20,21,31-34], would have substantial benefits at the population level according to economic modeling [35]. It is anticipated that the majority of students in the year group of participating schools will take part in the study, based on participation rates found in previous school-based trials conducted by the research team [36-39]. To account for school dropouts during the trial, which are expected to be approximately 10% based on similar previous school-based trials [40], this study will recruit 14 schools (with at least 840 students).

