### Statistical Analysis

Analyses will use an intention-to-treat approach, including all available measurements for all students, in the groups in which they were randomized. Baseline equivalence and attrition between groups will be examined using single-level analyses, one-way analyses of variance to examine normally distributed data, chi-square analyses to examine binominal data, and Mann-Whitney *U* tests to examine nonnormally distributed data. The baseline data of the primary outcomes will be used as covariates to ensure that any differences between groups at baseline are accounted for. To examine intervention by time interaction–effects, mixed-effects regression will be used because of the multi-level nature of the data (students nested within schools). Hypothesized intervention effects will primarily be examined using mixed-effects linear regression analyses for normally distributed data and mixed-effects logistic regression analyses for categorical data. Bonferroni adjustments will be made for multiple comparisons where appropriate. Multiple imputation and regression weighting strategies will be used to examine the impact of attrition. Sensitivity analyses will be used to assess the effect of attrition on inferences drawn from the target parameters in the statistical analyses**.**

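### Holm's step-down procedure would control the same family-wise error as the named Bonferroni adjustment and never reject less: a cheap efficiency gain, not an error

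*Protocol article*

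**What the plan says.** The only multiplicity text is one sentence in the Statistical Analysis section: "Bonferroni adjustments will be made for multiple comparisons where appropriate". It names the method but gives no family, number of tests or divisor.

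There is more than one test to which it could apply. The Aims, Objectives, and Hypotheses section numbers four hypotheses without ranking them. The abstract opens its list with "The primary outcomes of the trial will be the self-reported use of alcohol and drugs, anxiety and depression symptoms" and goes on to knowledge, motives for not drinking and willingness to seek help. The Primary Measures section places several instruments under some of these domains; the mental health part alone has the Kessler 6, PHQ-8 and GAD-7.

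The Sample Size Calculations section makes no mention of adjustment: "This would achieve 80% power to detect a standardized between-group mean difference of 0.2 in outcomes at the end of the trial". The significance level it gives for this is .05.

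**The concern.** Taken at its usual meaning, Bonferroni compares every p-value in a family of m tests with .05/m. Holm uses .05/m only for the smallest p-value and relaxes the threshold after each rejection. It needs nothing but the p-values, so it works unchanged with the planned mixed linear and logistic models.

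The authors hypothesize benefit on four fronts. If two or more effects in a family are real, the single-step rule will sometimes call a real effect non-significant where Holm would not, at the same error guarantee. The power statement is made at .05, so any adjustment is paid for out of the stated 80%.

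**Working it through.** **The plan's own figures.** The school inflation reproduces. The section requires "6 schools (with at least 60 students) in each of the 2 intervention groups were required", which is 12 schools. For school dropout, "which are expected to be approximately 10% based on similar previous school-based trials", 12/(1 − 0.10) = 13.3, rounded up to 14 schools, and 14 × 60 = 840 students.

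The 80% power cannot be checked, because the article gives no intracluster correlation (ICC), no within-student correlation and no sidedness. With 6 × 60 = 360 per arm and clustering ignored, the standard error is √(2/360) = 0.0745, so 0.2/0.0745 = 2.683 and two-sided power is Φ(2.683 − 1.960) = 76.5%. An assumed ICC of 0.01 gives a design effect of 1 + 59 × 0.01 = 1.59 and power of 56.7%. Adding an assumed baseline correlation of 0.7 brings it to 84.6%. So 80% is neither confirmed nor refuted, and it is taken as given below.

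**Why Holm never rejects less.** Order the p-values p(1) ≤ … ≤ p(m). Holm compares p(k) with .05/(m − k + 1), stopping at the first failure. Every threshold is at least .05/m, so any p-value that passes Bonferroni also passes Holm.

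**Why the error rate is the same.** Let m0 nulls be true. The first true null that Holm rejects is met at step m − m0 + 1 or earlier, where the threshold is at most .05/m0. The chance that any of m0 true-null p-values falls below .05/m0 is at most m0 × .05/m0 = .05. No assumption about dependence is used.

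**Size of the gain.** Inputs:
- 80% power per test at .05 (Sample Size Calculations); two-sided is assumed.
- Four tests in the family (assumed; this is the number of hypotheses, but the article does not make it the divisor).
- Correlation between test statistics of 0, 0.3 and 0.6 (assumed range).

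The mean of each test statistic under a real effect is 1.960 + 0.842 = 2.802. Bonferroni uses .05/4 = .0125, critical value 2.498, so power is Φ(2.802 − 2.498) = Φ(0.304) = 61.9%, whatever the correlation or the number of real effects.

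Holm was simulated with 500,000 replicates per setting:

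| Real effects (of 4) | Bonferroni, power per real effect | Holm, power per real effect |
|---|---|---|
| 1 | 62% | 62% |
| 2 | 62% | 64.1-64.6% |
| 3 | 62% | 66.8-67.8% |
| 4 | 62% | 70.6-72.7% |

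The ranges run from correlation 0.6 (low end) to 0 (high end), so correlation slightly reduces Holm's gain.

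With all four effects real, at correlation 0 / 0.3 / 0.6:
- Rejecting all four: Bonferroni 14.7% / 24.6% / 35.0%; Holm 38.3% / 47.1% / 55.7%.
- At least one rejection: 97.9% / 93.0% / 85.8% for both.

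With no real effect, family-wise error is 4.9% / 4.7% / 4.0% for both; it stayed below 5% in every setting. In no replicate did Bonferroni reject a hypothesis that Holm did not.

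**The case against.** The strongest objection is that Bonferroni is valid, widely accepted and correctly named, so there is no error to report. That stands: this is a matter of efficiency only.

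A reader might go further and infer that the plan throws away power on its four co-equal hypotheses for nothing. The article does not support this, for three reasons.

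- It never ties the adjustment to the four hypotheses. The sentence is qualified and could cover the two follow-up times, scales within a domain, or all primary outcomes. The abstract lists five primary domains, not four. The family may be settled in an analysis plan that is not shown.
- The largest gain needs all four effects to be real with equal power. The Strengths and Limitations section itself warns that change in substance use may be hard to assess at this age. With two real effects of four, the gain is 2-3 points; with one, essentially none. Nor does the article require all four to be significant, so the figures for rejecting all four are illustrative only.
- Bonferroni buys something: simple simultaneous confidence intervals for every effect, which Holm does not provide as easily.

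A further objection is that rewriting the sentence could widen the family by accident. This also stands. With an assumed family of sixteen tests, all effects real, Holm gives about 53-55% per test (100,000 simulated sets), below the 62% of Bonferroni over four. The size of the family matters more than the choice between the two procedures.

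None of this touches the core claim, which holds for any family of two or more tests.

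**Conclusion.** The point holds as an optional, low-cost improvement. Bonferroni is a sound choice; Holm is at least as good for every test decision at the same error rate.

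Under the assumed four tests with 80% power each, Holm adds about 0 points per real effect if one is real, 2-3 if two, 5-6 if three and 9-11 if all four. It does not raise the chance of at least one finding. Nor does it recover the full 18 points between 80% and 62%: at best it reaches 71-73%.

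That Holm never rejects less rests on no assumption about the family or the correlations. The percentages rest on four tests, two-sided .05, equal power and the stated 80%, which cannot be verified from the article.

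**What to change.** In the Statistical Analysis section, change only the procedure: say Holm (step-down Bonferroni) adjustments in place of Bonferroni adjustments, and leave the family as the team already intends it. Add that Holm-adjusted p-values will be reported with confidence intervals labelled as unadjusted.

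The cost is a few words, with no new data, sample size or modelling. The Results section says baseline assessments are still under way, so the change can be made before any outcome comparison.

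The downside is in the intervals. Simultaneous intervals that match Holm are less simple than Bonferroni's, and an unadjusted 95% interval may exclude zero while the adjusted p-value exceeds .05; the label is there to prevent misreading. If the team values simple simultaneous intervals above the extra rejections, keeping Bonferroni is defensible.

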## Results

This study was funded by an Australian Rotary Health Bruce Edwards Postdoctoral Research Fellowship from 2019 to 2022. Some of the development costs for the Mind your Mate intervention came from a seed funding grant from the Brain and Mind Centre, The University of Sydney. The enrollment of schools began in July 2020, with 12 of 14 schools enrolled at the time of submission. Baseline assessments are currently underway, and the first results are expected to be submitted for publication in 2022.

## Discussion

### Principal Findings

This protocol outlines the design of a cluster RCT to evaluate the effectiveness of an mHealth peer intervention for preventing mental health symptoms and alcohol and other drug use and promote help seeking and knowledge among adolescents. To our knowledge, the proposed intervention is the first peer-prevention program delivered via a mobile app facilitated through the school system. If effective, it has the potential for widespread implementation at a relatively low cost, as it uses a delivery method that is both acceptable and easily accessible to adolescents.

### Strengths and Limitations

The key strengths of the proposed effectiveness study are the intervention’s focus on fostering peer support among adolescents and the use of digital technology. The principle of peer support embedded within the intervention aims to strengthen and foster adolescents’ social connections both within their peer groups and with trusted adults. Social connection is known to be a key protective factor for mental health problems [57,58]. Furthermore, help seeking for mental health, drug, and alcohol concerns has long been plagued by surrounding stigma and a lack of knowledge of relevant support services; thus, most young people do not seek support when it is needed [24,59]. The provision of easily accessible information in the Mind your Mate smartphone app that destigmatizes common mental health challenges and provides support options might help overcome some of these barriers and encourage early help seeking in adolescents. Indeed, programs aimed at reducing mental health stigma are associated with increased confidence among young people in supporting peers [27]. Future research may more closely examine the interaction between stigma and peer-based processes.

Web-based delivery and the use of a mobile app means that the intervention is easily accessible and uses a delivery platform with which adolescents are familiar and comfortable. It also provides the potential to deliver the intervention widely at a relatively low cost, as no teacher training is required. The app itself is self-paced and can be used by students in their own time, with only a short time requirement anticipated for teachers. Furthermore, the web-based mode of delivery of the intervention ensures the fidelity of high-quality information and facilitates ease of access.

Another benefit of the program is its links to existing school health and physical education curricula, meaning schools could act as key delivery partners to roll out the intervention if found to be effective. Finally, the intervention was collaboratively designed with young people, meaning it is more likely to be acceptable and engaging for young people, an important outcome not only within the context of the current trial but also for future efforts to take the program to scale.

One limitation of the study is the reliance on participant self-report to collect data for the primary outcomes of this trial. Although these were chosen due to ethical and feasibility considerations and these are standard practices in school-based trials of mental health and substance use prevention [20,60], it is possible that measures of mental health and/or substance use could be subject to underreporting or overreporting. To mitigate these effects, students are reminded of the confidentiality of their responses at each survey occasion and encouraged to be as honest as possible, thereby reducing the risk of bias or concealment. Owing to time and budget constraints, the study was unable to provide smartphones to students who did not own them. Future research may adapt the intervention to be suitable for a range of groups, including adolescents living in rural and regional areas and adolescents experiencing technology barriers such as lack of access to smartphones and computers. Furthermore, although there is some evidence that digital tools may be more effective for certain users when human support is included compared with standalone tools [61], this was beyond the scope of this study because of time and budget constraints. Future research may explore the addition of human support or check-ins for peer-led mHealth programs and their impact on outcomes and user engagement. Finally, given the age of the students in the study (14-15 years old), we may be limited in our ability to assess change in substance use over the period of the trial, as the proportion of students using substances at this age may be small and typically tends to increase in later adolescence. Nonetheless, the Mind your Mate intervention was developed as a prevention approach because of the importance of early intervention, before thoughts and behaviors have become entrenched.

### Conclusions

The development of a novel mHealth tool for young people to support their peers and improve their own mental health represents an innovative applied approach to the prevention of mental disorders in a real-world setting. If effective, the intervention is low cost and will link to the existing high school syllabus, with the potential for widespread implementation and significant impact.

## Appendix

Multimedia Appendix 1 App-specific knowledge questionnaire.

## Abbreviations

CONSORT: Consolidated Standards of Reporting Trials
mHealth: mobile health
NSW: New South Wales
RCT: randomized controlled trial
REDCap: Research Electronic Data Capture
